#### Primary endpoints

The primary endpoints will be met if the following criteria are achieved:Dose sufficiencyIf the majority of treated patients achieve a serum 25OHD of 80 nmol/l at both 12 and 24 months and the average serum 25OHD for treated patients is > 75 nmol/l at 12 and 24 monthsDose adherenceIf patients take > 80% of the prescribed monthly doseSafetyCalcium [40]■ If the mean serum calcium concentration in each patient is <2.75 mmol/L (11 mg/dL) over the course of the study.■ If there is no increase in the prevalence of hypercalcaemia relative to the baseline prevalence.■ If the urine calcium excretion in each patient is less than 7.5 mmol/24 h OR the mean urinary calcium-creatinine ratio in each patient is <1.0 (when calcium and creatinine are measured in mmol) over the course of the study.■ If there is no increase in the prevalence of hypercalciuria relative to the baseline prevalence.Kidney function■ If there is no greater than a 20% fall in the average estimated GFR [GFR = 186.3 × SerumCr^-1.154^ × age^-0.203^ × 1.212 (if patient is black) × 0.742 (if female) – MDRD formula (21)] over the course of the study.■ If the average eGFR at the end of the study is no more than 20% less in vitamin D treated patients than in placebo treated patients.Renal calculiIf no more than two episodes of renal calculus occurs in vitamin D treated patients during the course of the study.

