### Sample size and randomisation

The design of the study is an optimal two-stage phase II trial using the approach of Simon [41]. Sample sizes are determined separately for the two cohorts. The two cohorts, those receiving vitamin D and those receiving placebo, will be analysed separately. Assuming a lower limit of efficacy of 48% and a regimen activity level of 68%, the study would proceed in two stages. In the first stage, if more than 7 patients with serum 25OHD less than 80 nmol/l are observed in the first 14 patients in the active arm, consideration will be given to either modifying the regimen or stopping the study due to inactivity.

Twenty-five patients (in a 2:1 randomisation) will be accrued to the placebo arm to allow adequate data to estimate concentration of serum 25OHD in an untreated cohort. Thus it is proposed to accrue a total of 75 patients into the study, 50 receiving vitamin D and 25 receiving placebo. These calculations are based on power of 80% with 95% confidence and allow for a modest dropout rate.

Patients will be centrally randomised by the Australian National Health and Medical Research Council (NHMRC) Clinical Trials Centre using a computerised interactive voice response system (IVRS). Patients will be stratified by gender.

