### Statistical methods

Analysis of primary endpointsThe percentage of patients achieving a serum 25OHD above 80 nmol/l at 12 and 24 months receiving treatment will be reported. Summary statistics of serum 25OHD concentrations will be reported for both groups at 12 and 24 months.Dose adherence will be reported as the percentage of dose taken compared to the prescribed monthly dose as calculated from the patient diary and study forms. A 95% confidence interval will be reported to check if the expected rate of 80% dosage of study tablets for the duration of the study protocol by all patients is obtained.Safety outcomes will be reported as the proportions of patients exceeding the following maxima, as well as summary statistics where appropriate.Analysis of secondary endpointsParticipation rate will be reported as the proportion of subjects eligible and invited to participate who agree to be randomised. A 95% confidence interval will be reported to check if the expected rate of 60% was obtained.Progression free survival will be displayed using Kaplan-Meier survival curves.

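### The between-arm kidney criterion compares end-of-study average eGFR without using the baseline eGFR already collected, which costs precision when the true deficit is near the 20% limit

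*Protocol article*

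**What the plan says.** The Primary endpoints section lists criteria that must be achieved for the primary endpoints to be met. Two concern kidney function.

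- Between arms: "If the average eGFR at the end of the study is no more than 20% less in vitamin D treated patients than in placebo treated" patients.
- Over time: "If there is no greater than a 20% fall in the average estimated GFR" over the course of the study. No arm is named.

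Table 3 schedules eGFR at baseline, 8, 16 and 24 months. Under Sample size and randomisation the plan is to "accrue a total of 75 patients into the study, 50 receiving vitamin D and 25 receiving placebo", and "Patients will be stratified by gender"; neither eGFR nor age is a stratification factor. For the safety analysis, Statistical methods says only: "Safety outcomes will be reported as the proportions of patients exceeding the following maxima, as well as summary statistics where appropriate". The inclusion criteria require an eGFR in the laboratory's normal range at entry.

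**The concern.** eGFR differs persistently between patients, so a patient's 24-month value depends heavily on the value at entry. A comparison of end-of-study averages leaves that between-patient variation in the error term. With only 25 placebo patients, chance differences at entry make up a sizeable part of the error.

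This is the only kidney criterion with a control group, so it is the one that answers the stated objective of no clinically significant renal difference between the arms. At stake is how well the rule separates a true deficit somewhat above 20% from one somewhat below it. A wrong pass is the costlier error, because the Discussion part of the abstract says favourable outcomes will form the basis of a phase III study.

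**Working it through.** **The plan's own figure.** The stated sample size concerns 25OHD, not eGFR. With 48% and 68% as the two rates, one-sided alpha of at most 0.05 and power of at least 80%, an exact search for Simon's optimal design gives 14 patients in stage 1 and 46 in all (alpha 0.044, power 0.805). Allowing about 8% dropout, 46/0.92 = 50. So the 14 and the 50 both reproduce, but neither says anything about the eGFR criterion, for which no power is stated.

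**Inputs for eGFR.** From the protocol: 50 v 25 patients and a limit ratio of 0.80, ln(0.80) = −0.223. Assumed, because the protocol gives no figures: between-patient SD 0.20 on the log scale (range 0.15 to 0.25) and baseline to 24-month correlation r = 0.8 (range 0.5 to 0.9). The log ratio is treated as normal.

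**Standard error of the arm difference.**

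- Unadjusted: 0.20 × √(1/50 + 1/25) = 0.20 × 0.245 = 0.049.
- Adjusted for baseline: 0.049 × √(1 − 0.8²) = 0.029; 0.042 at r = 0.5 and 0.021 at r = 0.9.

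**Size of chance imbalance.** 95% of trials have a baseline difference within 1.96 × 0.049 = 0.096, which is 43% of 0.223. At r = 0.8 about 0.8 × 0.096 = 0.077 carries through to 24 months, about a third of the limit.

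**True 25% deficit, probability of passing this criterion.** The distance to the limit is ln(0.80) − ln(0.75) = 0.0645.

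- Unadjusted: z = 0.0645/0.049 = 1.32, so 9.4%. Over the SD range: about 4% at 0.15 and 14.6% at 0.25.
- Adjusted: z = 0.0645/0.0294 = 2.20, so 1.4%; 6.4% at r = 0.5 and 0.1% at r = 0.9.

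**True 15% deficit, probability of failing.** The distance is ln(0.85) − ln(0.80) = 0.0606.

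- Unadjusted: z = 1.24, so 10.8%.
- Adjusted: z = 2.06, so 2.0%; 7.7% at r = 0.5.

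**Away from the limit, unadjusted rule.**

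- No true difference: z = 0.223/0.049 = 4.55, a failure about 3 times in a million.
- True 10% deficit: z = (ln 0.90 − ln 0.80)/0.049 = 0.1178/0.049 = 2.40, so 0.8%.

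**Check on the arithmetic scale.** Assume mean 90 and r = 0.7, with SE = SD × √(1/50 + 0.64/25) = SD × 0.2135. For a true 25% deficit the distance to the limit is 0.05 × 90 = 4.5.

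- SD 15: z = 4.5/3.20 = 1.40, so 8.0%, falling to 2.5% with adjustment.
- SD 20: z = 4.5/4.27 = 1.05, so 14.6%, falling to 7.0%.

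The pattern is the same.

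**The companion fall criterion.** Suppose it applies to the treated arm, that arm truly falls by 25% and placebo is stable. The SE of the mean log change is 0.20 × √(2(1 − r))/√50 = 0.0179 at r = 0.8. A 25% fall then passes this rule alone with z = 0.0645/0.0179 = 3.61, or 0.015%. Passing both kidney rules has probability about 0.004% at r = 0.8 and 0.3% at r = 0.5. If the rule is instead read over all 75 patients, the same fall averages (50 × 25% + 25 × 0%)/75 = 16.7%, which passes.

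**The case against.** Several points on the other side stand.

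- **Adjustment may be settled elsewhere.** The text says average eGFR and neither requires nor excludes adjustment, and covariates are often left to an analysis plan, which is not shown here. This bars any claim that the plan forbids adjustment. It does not remove the point: the pass/fail quantity itself is fixed in the protocol, and its plain reading is unadjusted averages. Elsewhere the same list does refer to baseline, for hypercalcaemia and hypercalciuria.
- **The fall criterion uses baseline.** On the treated-arm reading it catches nearly all the wrong passes computed above, more than adjustment of the between-arm rule would. A reader might take 9.4% as the chance that kidney safety as a whole is wrongly passed; that is not supported, since both criteria must be met. The protection is uncertain, however, because the criterion names no arm and has no control, so it cannot separate a drug effect from drift.
- **Chance imbalance alone does not decide the verdict.** A reader might infer that the regimen could fail merely because of who was randomised. With no true effect that is a matter of about 3 in a million.
- **There is no bias.** A reader might infer that the wrong quantity is estimated, or that the 2:1 allocation distorts it. Randomisation keeps the unadjusted difference unbiased, and the allocation only sets the standard error.
- **Spread may be smaller than assumed.** Normal-range entry may reduce both the SD and the correlation. Stratification by gender already largely balances the sex factor in the eGFR formula, so baseline eGFR is the covariate that matters.

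**Conclusion.** The point holds as a loss of precision, not as an error that invalidates the safety endpoint. The gain from adjustment is confined to true deficits in the neighbourhood of 20%. There, under the central assumptions, it removes most of the misclassification on this criterion; at r = 0.5 it removes only about a third (a wrong pass at a true 25% deficit falls from 9.4% to 6.4%). Every eGFR figure rests on an assumed SD and correlation, on full follow-up of 50 and 25 patients, and on this criterion being taken alone. Losses would raise the error rates of either rule; the article already reports 10 patients who ceased for recurrence. Because the improvement uses data already scheduled, it is worth making even though the consequence is modest.

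**What to change.** Keep the 20% limit and state that the between-arm criterion is judged on the baseline-adjusted vitamin D / placebo ratio of eGFR at 24 months. Obtain it from an ANCOVA of log eGFR at 24 months on treatment, with log baseline eGFR and gender (the randomisation stratum) as covariates. Report the unadjusted arm averages alongside.

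The cost is one sentence of analysis text, with no added visits, tests or patients. The small downside is that the criterion becomes a ratio of adjusted geometric means instead of a ratio of arithmetic averages, so the wording of the criterion should say so.

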### Participant follow-up

Participation in this study is voluntary; patients will be able to withdraw at any time. Patients will be asked to present for clinical follow-up four monthly for the two years following treatment of their primary melanoma. Those who withdraw from treatment will be asked to continue follow-up visits according to the protocol even though they have stopped treatment, to allow collection of outcome data. If a patient decides to stop their follow-up visits, their health status will be periodically ascertained by way of phone contact with their general practitioner or by direct phone contact. The National Death Index at the Australian Institute of Health and Welfare will be used to collect survival information on patients who have been lost to follow-up.

After completion of active follow-up, recurrences will be ascertained through the New South Wales Central Cancer Registry and deaths through the National Death Index for a period of five years after date of diagnosis.

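### The renal-calculus objective is a difference from placebo, but its only criterion is a count of episodes in the vitamin D arm, so meeting or failing it does not answer the objective

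*Protocol article*

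**What the plan says.** Under Objectives of the present trial, the renal-calculus objective is comparative: no clinically significant difference in incidence between the active and placebo groups.

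Under Primary endpoints (Safety, Renal calculi), the endpoint counts as met if "no more than two episodes of renal calculus occurs in vitamin D treated patients during the course of the study". No placebo count, margin or confidence limit appears. In the same list, one of the two kidney-function criteria does compare the arms: it sets mean eGFR at the end of the study in vitamin D patients against that in placebo patients.

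Under Sample size and randomisation, the arms are "50 receiving vitamin D and 25 receiving placebo". Under Participant follow-up, both arms are seen over the same period: "Patients will be asked to present for clinical follow-up four monthly for the two years following treatment of their primary melanoma".

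Under Statistical methods, the safety plan is descriptive: "Safety outcomes will be reported as the proportions of patients exceeding the following maxima, as well as summary statistics where appropriate". It does not mention comparing calculi between arms.

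**The concern.** The objective and the rule that is meant to decide it concern different quantities. The objective needs two incidences and their difference. The rule needs one count from one arm. It also counts episodes, so three episodes in one patient would fail it although only 1 of 50 patients is affected.

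Safety is one of the primary endpoints, and the abstract says that favourable outcomes will form the basis for a multi-centre phase III study. A met criterion could be carried forward as the answer to the comparative objective although no comparison was made. A failed one could count against the regimen when placebo patients had as many calculi or more. Because the protocol itself fixes the rule, an analysis plan consistent with it would inherit the mismatch.

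**Working it through.** **Inputs.** From the protocol article: 50 vitamin D and 25 placebo patients, a limit of two episodes in the vitamin D arm, and two years of follow-up. Assumed here: all 50 patients are followed for two years, with at most one episode each, so that episodes and patients coincide. The article gives no expected calculus rate, and none is needed below.

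**Where the 50 comes from.** The sample size rests on serum 25OHD: "Assuming a lower limit of efficacy of 48% and a regimen activity level of 68"%. An exact search for Simon's optimal two-stage design with p0 = 0.48, p1 = 0.68, one-sided alpha 0.05 and power 80% gives n1 = 14, r1 = 7, n = 46, r = 27 (exact alpha 0.044, power 0.805). The figures 14 and 7 are those in the article, although the search counts successes and the article counts failures. An assumed dropout of 8% gives 46/(1 - 0.08) = 50; the article says only that dropout is modest. So 50 is the planned denominator, chosen for 25OHD. The two-episode limit has no stated rate, margin or operating characteristics to reproduce.

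**Does the verdict follow the objective?**

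| Vitamin D | Placebo | Difference | Two-sided Fisher p | Criterion |
|---|---|---|---|---|
| 2/50 (4%) | 0/25 (0%) | +4 points | 0.55 | met |
| 3/50 (6%) | 3/25 (12%) | -6 points | 0.39 | failed |

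The row with an observed excess on vitamin D passes, and the row with fewer calculi on vitamin D fails. Neither difference is statistically clear. The point is only that the verdict ignores the placebo column.

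**What 2/50 says about incidence.** The Clopper-Pearson 95% interval is 0.5% to 13.7%. With fewer evaluable patients (assumed), the upper limit is 15.1% at n = 45 and 16.9% at n = 40.

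**How often the criterion is met.** P(X ≤ 2) = (1-p)^50 + 50p(1-p)^49 + 1225p²(1-p)^48. At p = 0.05 this is 0.077 + 0.202 + 0.261 = 0.54.

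| True two-year incidence | 1% | 2% | 4% | 5% | 8% | 10% | 14% |
|---|---|---|---|---|---|---|---|
| Probability that the criterion is met | 99% | 92% | 68% | 54% | 23% | 11% | 2% |

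**The comparison that the objective asks for.** Newcombe's interval combines the Wilson limits, which are 1.1% to 13.5% for 2/50 and 0% to 3.84/(25 + 3.84) = 13.3% for 0/25.

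- Lower limit: 0.040 - √[(0.040 - 0.011)² + (0.133 - 0)²] = -0.096.
- Upper limit: 0.040 + √[(0.135 - 0.040)² + (0 - 0)²] = +0.135.

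So 2/50 against 0/25 gives +4.0 points (95% CI -9.6 to +13.5). With one placebo patient affected (2/50 against 1/25), the difference is 0 (-15.8 to +10.0). Against 0/25, it takes 8/50 for two-sided Fisher p < 0.05 (p = 0.046).

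**The case against.** The strongest defence is that a fixed count is a sensible screen in a small pilot. Patients with a known history of calculi are excluded, and the rule fails the regimen about 89% of the time at a true 10% and 98% at 14%. A comparison with 25 placebo patients decides almost nothing: at the pass boundary its upper limit (+13.5 points) is practically the single-arm one (13.7%). The article states no margin for calculi against which to judge an interval. Counting episodes can only make the criterion harder to meet, the dose-cessation rule in Appendix 2 limits repeat episodes on treatment, and safety reporting is in any case planned as proportions of patients. The phase III trial would assess safety again. Tabulating both arms with intervals is commonly left to the analysis plan.

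Most of this stands as a defence of the count as a screen, and low power for a rare event is inherent in a trial of this size. It does not reconcile the count with the objective. The omission of a table would be no finding. Here, though, the protocol states when the endpoint is met, and that rule leaves out the arm that the objective names. The eGFR criterion shows that a comparative rule was within reach.

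A reader might infer four stronger points that the documents do not support:

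- That the rule tolerates an incidence of 14%. The 13.7% is a confidence limit for an observed 2/50; at a true 14% the criterion is met about 2% of the time.
- That the trial falls short of a promised 80% power for calculi. The sentence "These calculations are based on power of 80% with 95% confidence and allow for a modest dropout rate" belongs to the 25OHD design and claims nothing about calculi.
- That comparing the arms is ruled out by "The two cohorts, those receiving vitamin D and those receiving placebo, will be analysed separately". That sentence stands in the 25OHD sample-size text, and the eGFR criterion compares the arms. It needs no edit for this point.
- That the protocol treats two or fewer episodes as proof of no difference. It says only that the endpoint will be met.

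**Conclusion.** The point holds as a mismatch between an objective and its only criterion. The objective is a between-arm difference in incidence; the criterion is a single-arm count of episodes that is met or failed whatever the placebo result. It can be met at 2/50, where the data are compatible with a two-year incidence of 0.5% to 13.7% and, with 0/25 on placebo, with a difference of -9.6 to +13.5 points. It is met more often than not at a true incidence of 5% and seldom at 10% or above. It therefore works as a screen against a gross excess and is no evidence of similarity to placebo.

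The mismatch itself rests on the text alone. The figures assume 50 patients fully followed and at most one episode each. Full follow-up is optimistic: the Discussion reports that 10 patients, arm not given, had a recurrence and ceased the trial. Fewer evaluable patients would widen the intervals.

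**What to change.** 1. Define the renal-calculus endpoint as the number of patients with at least one calculus in each randomised arm. Report the between-arm risk difference with a Newcombe or exact 95% confidence interval; episodes can be listed as well.
2. Base any statement on the comparative objective on that interval, and say that the trial cannot exclude an excess up to its upper limit.
3. Keep the two-episode limit as a single-arm screening limit for the vitamin D arm, and state that meeting it does not by itself show absence of a difference from placebo.

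The change is one of wording and reporting. Calculi are already a safety endpoint, and both arms have the same follow-up schedule, so no extra patients or visits are needed. The cost is a wide interval and a less reassuring safety statement. The comparison will not be decisive at this size and should be presented as an estimate.

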#### Secondary endpoints

The secondary endpoints will be met if the following criteria are achieved:If 60% of eligible patients agree to participate and the study accrues 75 patients in 2 yearsImproved progression free survival

#### Other tests

A sample of baseline blood will be stored for later extraction of DNA and possible testing for gene variants (e.g. in the vitamin D receptor gene or the vitamin D binding protein gene) that may influence vitamin D activity to see if they influence plasma vitamin D response to therapy or melanoma recurrence.

## Methods/Design

### Trial design

This is a multi-center placebo controlled randomised phase II trial which aims to evaluate the safety and efficacy of high dose vitamin D therapy in patients who have been treated for primary melanoma and are at high risk of recurrence. Patients will receive treatment at Melanoma Institute Australia (MIA) (at the Poche Centre or at the Royal Prince Alfred Hospital (RPAH)), or other participating melanoma study centres.

### Participants

Eligible participants are patients aged 18 – 79 who have completed primary (surgical) treatment for cutaneous melanoma and are considered to be at high risk for recurrence: AJCC Stage IIb, IIc, IIIa (N1a, N2a), IIIb (N1a, N2a), that is, patients with ulcerated tumors thicker than 2 mm or with tumors thicker than 4 mm or those with nodal micro-metastases. Comprehensive inclusion and exclusion criteria are found in Appendix 1.

### Intervention

MaterialsStudy medications will be provided under the Australian Therapeutic Goods Administration Clinical Trials Notification scheme. Patients randomised to the active treatment arm will receive Cal.D.Forte tablets containing 50,000 IU of cholecalciferol from API Consumer Brands New Zealand. Patients randomised to the placebo arm will receive placebo tablets from a batch prepared by API for an unrelated study and provided by that study’s coordinator, [name], of the Menzies School of Health Research, Darwin.Study drug administrationPatients will receive oral vitamin D (Cal.D.Forte) tablets containing 50,000 IU of cholecalciferol from API Consumer Brands New Zealand or matching placebo.Following confirmation of eligibility and randomisation, patients randomized to active treatment will receive 500,000 IU of cholecalciferol (Vitamin D3) orally (10 tablets to be administered by the study team during the initial baseline study visit).Thereafter, patients will self-administer 50,000 IU, 1 Cal.D.Forte tablet on the 1st day of each month following commencement of treatment, for a period of 23 months.

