**Methods/Design:**

This is a pilot placebo-controlled randomised phase II trial to assess the feasibility, safety and toxicity of an oral loading dose of Vitamin D (500,000 IU) followed by an oral dose of 50,000 IU of Vitamin D monthly for 2 years in patients who have been treated for cutaneous melanoma by wide excision of the primary. Patients aged 18 – 79 years who have completed primary surgical treatment and have Stage IIb, IIc, IIIa (N1a, N2a) or IIIb (N1a, N2a) disease are eligible for randomisation 2:1 to active treatment or placebo. The primary endpoints are sufficiency of dose, adherence to study medication and safety of the drug. The secondary endpoints are participation and progression free survival. The study has been approved by the Ethics Review Committee (RPAH Zone) of the Sydney Local Health District, protocol number X09-0138.

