**Physiology of vitamin D.**

#### Serum measurement of vitamin D

Serum 1α,25OHD has a very short half-life and is not a good measure of vitamin D status [8]. Serum 25OHD is the main circulating form of vitamin D. It is relatively stable [9], has a long half-life (τ1/2 = 18.9 +/- 3.1 days) [10] and provides the substrate for local production of the active hormone, 1α,25OHD and is therefore considered the best indicator of vitamin D status [11].

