### Objectives of the present trial

To determine whether administration of a loading dose of oral vitamin D_3_ (500,000 IU) followed by a monthly tablet of 50,000 IU of oral vitamin D_3_ for 2 years following primary treatment of melanoma at high risk of recurrence:achieves maintenance of serum 25 hydroxyvitamin D concentrations above 80 nmol/l in patients who receive active treatmentachieves > 80% adherence to dosing rates during 2 years of study treatmentachieves adequate recruitment rates (75 patients in 2 years from one site)produces no clinically significant difference in hypercalcaemia incidence between the active and placebo groupsproduces no clinically significant difference in renal function between the active and placebo groupsproduces no clinically significant difference in the incidence of renal calculi between the active and placebo groups

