### Assessment of outcome

Dose sufficiencyThe short term effects of high dose vitamin D therapy will be assessed by conduct of the following assays and diagnostic tests:Renal and liver function tests (including estimated Glomerular Filtration Rate (eGFR) and urine calcium/creatinine ratio)Serum 25OHD levelsSerum corrected calcium, 24 hour urinary calcium excretion or urinary calcium to creatinine ratio.The scheduling of these assessments is found in Table 1.AdherencePatients will be asked to keep a diary to record their use of the study drug. These diaries will be reviewed four monthly at each patient follow-up visit.The study team will confirm adherence to the treatment regime by contacting study patients at interim time points during the treatment phase and also during clinic follow-up visits at 4, 8, 12, 16, 20 and 24 months. To help improve adherence, monthly SMS text messages will be sent to those patients with mobile phones, reminding them to take their study tablets.In the event of a missed dose, patients will be able to take the missed dose at the following clinic visit. Appropriate procedures will be established to facilitate this while ensuring maintenance of necessary “blindness” with respect to the intervention arm each participant is in.SafetyThe feasibility, safety and short term effects of high dose vitamin D therapy will be assessed by the conduct of the assays and diagnostic tests found in Table 3.

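### The tablet calendar and the 25OHD sampling dates are not aligned: read literally, the 24-month sample comes about a month later after the last tablet than the 12-month sample, which biases half of the dose-sufficiency endpoint towards failure

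*Protocol article*

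**What the plan says.** **Dosing.** The Intervention section gives the loading dose at baseline ("10 tablets to be administered by the study team during the initial baseline study visit") and then "1 Cal.D.Forte tablet on the 1st day of each month following commencement of treatment, for a period of 23 months". The Abstract describes "an oral dose of 50,000 IU of Vitamin D monthly for 2 years" and the Objectives say "followed by a monthly tablet of 50,000 IU of oral vitamin D_3_ for 2 years".

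**Sampling.** Assessment of outcome lists "clinic follow-up visits at 4, 8, 12, 16, 20 and 24 months". Table 3 places serum 25OHD at baseline, 4–6 weeks, 4, 12 and 24 months. Neither place relates the blood draw to a tablet. Assessment of outcome also lets a missed tablet be taken at the following clinic visit, without saying whether blood is drawn first.

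**Endpoint.** Dose sufficiency is a primary endpoint. It is met if "the majority of treated patients achieve a serum 25OHD of 80 nmol/l at both 12 and 24 months" and the treated mean exceeds 75 nmol/l at both times. The Objectives describe the aim as maintaining concentrations above 80 nmol/l.

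**Kinetics.** The Background states that serum 25OHD "has a long half-life (τ1/2 = 18.9 +/- 3.1 days").

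**The concern.** The criterion must hold at both visits and uses the same thresholds at each, so it presumes that the two samples are taken at a similar point after dosing. A fixed count of 23 tablets on calendar firsts does not give that. A patient who starts mid-month has a short first interval, and the slack reappears after the last tablet, just before the 24-month draw.

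If the late draw lowers 25OHD, a regimen that holds patients above 80 nmol/l throughout treatment could miss the 24-month half of the endpoint. A fall from 12 to 24 months could also be read as waning effect or poor adherence when it comes from the calendar. According to the Abstract, favourable outcomes of this pilot are to form the basis of a phase III trial.

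**Working it through.** **Inputs.** Tablets on the 1st of months 1 to 23 after the baseline month (Intervention, literal calendar reading). Visits at baseline + 12 and + 24 calendar months (Table 3). Half-life 18.9 ± 3.1 days, that is 15.8 to 22.0 (Background). Start dates from December 2010 to August 2014 (accrual period in the Abstract).

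**Check on the half-life.** Five half-lives are 5 × 18.9 = 94.5 days. This agrees with the article's statement that daily dosing takes about 3 months to reach a plateau.

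**One patient.** Baseline is 15 January of year 1. Tablet 1 is on 1 February of year 1 and tablet 23 on 1 December of year 2.
- 12-month visit, 15 January of year 2: last tablet 1 January, gap 14 days.
- 24-month visit, 15 January of year 3: last tablet 1 December, gap 45 days.

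**All start dates (1,370 days enumerated), under each reading of the dosing sentence.**

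| Reading | Gap at 12 months | Gap at 24 months |
|---|---|---|
| Calendar firsts, 23 tablets | 0–30 days, mean 14.7 | 28–61 days, mean 45.1; about 95% over 31 days |
| Monthly anniversaries of baseline, 23 tablets | tablet day: 0 days if dosed first, 28–31 if drawn first | 28–31 days |
| Calendar firsts, 23-month span after the first tablet (24 tablets) | 0–30 days, mean 14.7 | 0–30 days, mean 14.7 |

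On the first reading the 24-month draw is later by 45.1 − 14.7 = 30.4 days, one dosing interval. The last tablet itself covers about 30.4 of the 45.1 days, so the average overrun past the final interval is 45.1 − 30.4 = 14.7 days.

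**Effect on the tablet-derived part of 25OHD (first reading).** Assume mono-exponential decay. The ratio of the 24-month to the 12-month tablet-derived part is about 0.5^(extra days ÷ half-life).
- Half-life 18.9 days: 0.5^(30.4/18.9) = 0.33.
- Half-life 15.8 and 22.0 days: 0.26 and 0.38.
- Assumed effective half-life of 40 and 60 days (not in the article), over a 30-day interval: 0.5^(30/40) = 0.59 and 0.5^(30/60) = 0.71. Full enumeration, which keeps the residue of the loading dose, gives 0.59 and 0.68.

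At 18.9 days, the share of the last tablet's own contribution still present at 24 months runs from 0.5^(28/18.9) = 36% to 0.5^(61/18.9) = 11%.

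**Effect on the majority criterion.** This needs a baseline 25OHD and a rise on treatment, and the article gives neither. For illustration only, assume a baseline mean of 55–65 nmol/l (SD 20), an average rise of 35 nmol/l (lognormal, SD 0.3 on the log scale), within-patient SD 8 and half-life 18.9 days. The simulated share at or above 80 nmol/l at both visits is then:
- 27–43% as scheduled;
- 58–72% if the 24-month draw has the same timing as the 12-month draw;
- 31–49% if both draws are troughs.

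With an assumed baseline mean of 75, the schedule as written gives 61%.

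**The case against.** **The ranges rest on one reading.** This stands in part. The first day of each month most naturally means the calendar date, but it can mean the first day of each study month. The 24-month sample is then an ordinary trough, and a 12-month sample drawn before that day's tablet would match it. The endpoint is still loosely fixed on that reading, because the 12-month visit falls on a tablet day with no stated order of draw and dose. Follow-up is also described as "four monthly for the two years following treatment of their primary melanoma". Counting visits from surgery rather than from the loading dose would bring the 24-month draw closer to the last tablet.

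**Draw timing belongs to the full protocol.** A missing visit window alone would be no finding in a condensed article. The point here arises from rules the article does state: 23 tablets on firsts of the month, visits at 12 and 24 months, and one criterion for both.

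**Consequences are limited.** This stands. The Data Safety Monitoring Committee's efficacy looks are at 4 and 12 months (Quality assurance), before the gap arises. Results are reported at both times, so the 12-month result stays visible. The bias runs against declaring success, and the sample size does not depend on it.

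**Stronger inferences that the documents do not support.**
- A reader might infer that two years and 23 months contradict each other. They need not: a loading dose at month 0 plus 23 monthly tablets makes 24 dosing occasions.
- A reader might infer that the 24-month sample measures washout, some 1.5 intervals after treatment ended. The 45 days run from the last tablet, and the overrun past its interval is about 15 days. Total 25OHD also includes the patient's own level, any supplements and residual dose. It is a late trough with partial decline.
- A reader might infer that the schedule turns a pass into a fail. The simulation does so only under some assumed inputs. Trough sampling at both visits also stays below a majority, so much of the contrast is between mid-interval and trough sampling.

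**Conclusion.** The concern holds as a timing mismatch in a primary endpoint. On the calendar reading, the 24-month sample is taken on average 30 days later after a tablet than the 12-month sample, and about 15 days past the last dosing interval. At the stated half-life, this leaves about one third of the 12-month tablet-derived rise (26–38% over the stated half-life range; about 59–71% for assumed half-lives of 40–60 days). The direction is towards failing the 24-month half of dose sufficiency and towards an apparent decline.

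The day counts rest on calendar-date dosing, visits counted from baseline and no catch-up tablet at the visit. The ratios also rest on mono-exponential decay. The size in nmol/l, and any effect on the majority or mean criterion, cannot be derived from the article.

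**What to change.** 1. Reconcile the tablet calendar in the Intervention section with the 24-month sampling date in Table 3, so that only one reading is possible. This review proposes no dosing rule.
2. State that the 12- and 24-month 25OHD samples are drawn at the same time since the last study tablet, within one dosing interval, and before any tablet taken at that visit.
3. Where that is not achieved, keep every sample in the endpoint as scored. Add a report or sensitivity analysis of 25OHD by days since last tablet, using the dosing diaries already kept. Late samples should not be excused when they fall below 80 nmol/l: that would drop failures while keeping successes, and on the calendar reading about 95% of start dates give a gap over 31 days.

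The cost is wording, a timing rule for blood draws already planned and one supplementary table. No extra patients or samples are needed. The small downside is that the final draw may fall a few weeks before the nominal 24-month date.
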